#### Quality of life data

Quality of life data will be collected using the EuroQol 5-dimension, 3-level (EQ-5D-3L) patient-reported outcome measures (PROM) [50]. This widely used, patient-completed PROM gathers generic data on health-related quality of life at specific time points when completed. The EQ-5D-3L is used on the advice of the NICE 2019 position statement, recommending its use over the new EQ-5D-5L [51]. Questionnaires will be completed at enrolment, week 4 and week 10 (study end).

#### Daily symptom tracker questionnaire

Participants will be required to complete a daily symptom tracker throughout the study period to identify the development of any symptoms that are indicative of a possible COVID-19, or other upper respiratory tract infection. The link for this will be sent to the participants daily via email.

#### Baseline assessment

Participant demographics including date of birth, gender and ethnicity will be recorded. Medical history will be recorded including current medical conditions, regular medications, and any allergies. Participants will be asked to complete a quality-of-life questionnaire: EQ-5D-3L, this will also allow for a later cost-effectiveness analysis as well as undergo the baseline blood tests outlined above. Randomisation and training in spray application will take place after baseline assessments and questionnaires have been completed, on the same day.

#### Adverse events

Adverse events are, according to the definitions, any unfavourable or unintended event affecting participants during the study. In cases of prolongation of hospitalisation, death or significant clinical sequelae, these events are defined as serious adverse events (SAEs), the occurrence of which the study sponsor (Swansea University) will be informed within 48 h of the initial observation of the event. The study treatment period is defined as the period from the first study-related nasal and throat spray administration until 14 days after the last study-related nasal and throat spray administration. Participants will be encouraged from the outset to contact the research team at the time of an event occurring by telephone or email and all details will be documented on the SAE form. The daily symptom tracker questionnaire will also provide an opportunity for symptom monitoring and the opportunity to report any symptoms that will be flagged up to the research team via a weekly report.

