#### Secondary outcomes

Severity and duration of symptoms (time taken for all symptoms to resolve, length of hospital and intensive care stay, mortality rate)Acquisition of non-COVID-19 respiratory viral infections, e.g. common cold or flu symptoms in non-COVID-19 positive participantsUsability and acceptability data of nasal and throat spray as prophylaxisEffect on quality-adjusted life years and cost-effectivenessSubsequent familial/household COVID-19 infectionBaseline haematological or questionnaire findings as predictors for acquiring COVID-19 infection or determining severity and/or duration of resultant infectionassociations between symptom severity and/or duration and prognosis with COVID-19

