#### Secondary outcomes

Our approach toward the secondary outcome analysis would be mainly exploratory and report the summary outcomes of the secondary outcome measures. We will check the distributions of the data whether following normal or not. For any continuous secondary outcomes (e.g. length of hospital stay, severity and duration of symptoms) we will report the mean and standard deviation, along with the outcome of statistical tests by groups (e.g. *t*-test). The categorical outcomes will be reported using percentages and chi-square tests. In all cases, a summary of the missing data will be reported. We will also report the safety data using summary statistics by the patients and the events for each of the trial arm groups.

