### Economic evaluation

An economic evaluation will be undertaken at day 70 post randomisation. The proposed secondary endpoints and methods for economic evaluation follow the guidance set out by NICE [54]. The primary economic analysis will be a cost-utility analysis expressed in terms of quality-adjusted life years (QALYs). Cost data based on the cost of a course of active ingredient spray will be obtained from the supplying company (Marinomed Biotech AG). A comparator cost analysis will be performed for the cost associated with developing COVID-19. A number of models will be developed, expressing the predicted cost of falling ill with COVID-19 but remaining at home, the cost associated with a short hospital stay and finally that associated with an admission to critical care. Treatment costs will include the cost of each scenario including healthcare professionals, equipment and infrastructure costs. Incremental cost-effectiveness ratios, incremental net monetary benefit and incremental net health benefit statistics will be calculated. A QALY in the range of £20,000–£30,000 will be considered acceptable in line with NICE guidance [54].

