### Revision to trial design

The trial protocol was written prior to the introduction of vaccines and was initially aimed to recruit healthcare professionals who have not been previously tested positive for COVID-19. However, the success of the UK vaccination programme and prioritisation of healthcare professionals for vaccines has meant that the majority of staff were no longer eligible for the trial. Approval was therefore sought from the Sponsor (Swansea University), REC and SBUHB (NHS) R&D Office to widen the potential pool of study participants to include all key workers or those needing to interact with people outside of their household for study or work from the 11th of January 2021. The full trial protocol is available on ClinicalTrials.gov [40].

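### As written, the SAE criteria omit a new unplanned hospital or intensive-care admission that ends in recovery, although the protocol uses hospital stay as a severity outcome and a cost scenario

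*Protocol article*

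**What the plan says.** The Adverse events section first defines an adverse event broadly, as anything unfavourable or unintended that happens to a participant during the study. It then sets the threshold for seriousness: "In cases of prolongation of hospitalisation, death or significant clinical sequelae, these events are defined as serious adverse events". For events that meet it, the sponsor "will be informed within 48 h of the initial observation of the event". The same section asks participants to contact the team when an event occurs and says the details go on the SAE form.

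Hospital care appears in three other places:

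- Outcomes, Secondary outcomes: "Severity and duration of symptoms (time taken for all symptoms to resolve, length of hospital and intensive care stay, mortality rate".
- Statistical analysis, Secondary outcomes: "For any continuous secondary outcomes (e.g. length of hospital stay, severity and duration of symptoms" introduces the measures to be summarised and tested by group. The section adds: "We will also report the safety data using summary statistics by the patients and the events", for each arm.
- Economic evaluation: the modelled scenarios include "the cost associated with a short hospital stay and finally that associated with an admission to critical care".

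On the population, Revision to trial design says that recruitment was widened to "all key workers or those needing to interact with people outside of their household for study or work". Recruitment/consent describes self-referral through posters, social media and the press.

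**The concern.** Prolongation presupposes a stay that is already under way. That criterion suits a trial in inpatients. Here the participants live at home, attend an enrolment visit and apply the spray themselves, so the hospital event to expect is a first admission. The rule does not name it.

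The omission matters because SAE status is what starts the 48 h notice to the sponsor. It also decides which events enter any summary of serious events by arm. A participant admitted with COVID-19 who recovers would count towards the severity outcome and correspond to a costed scenario, but would be classed as non-serious for safety purposes.

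**Working it through.** The point turns on wording, and the plan gives no figure to reproduce. The check applies the three stated criteria to the hospital events that could occur in a participant who starts the trial at home.

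| Event | Prolonged stay? | Death? | Significant sequelae? | SAE as written? |
|---|---|---|---|---|
| Admission ending in death | – | yes | – | yes |
| Admission leaving significant sequelae | – | no | yes | yes |
| Ward stay lengthened, for example by transfer to intensive care | arguably yes | no | no | arguably yes |
| New ward admission, full recovery | no | no | no | **no** |
| New admission directly to intensive care, full recovery | no | no | no | **no** |

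The last two rows are the gap. No other section of the article adds new admission to the list.

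Next, compare the severity markers in the secondary outcomes with the SAE criteria. Death is in both. Hospital and intensive-care stay are severity markers, but among the SAE criteria they appear only as prolongation. Any length of stay, and both hospital scenarios in the economic evaluation, presuppose an admission. The protocol therefore treats as a mark of severity something its safety rule does not treat as serious.

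Then consider the other reporting routes. Symptoms entered in the daily tracker reach the research team in a weekly report, and a tracker left incomplete prompts a telephone call only after more than 5 days. Both can be slower than 48 h, so neither replaces the sponsor notice.

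For scale, the only arithmetic available is an illustration:

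- Inputs from the sample size section: 152 participants per arm after losses, and infection rates of 25% and 12.5%.
- Expected infections: 152 × 0.25 + 152 × 0.125 = 38 + 19 = 57, whichever arm carries which rate.
- Assumed share admitted: 2–5%. The documents give no such figure.
- COVID-19 admissions: 57 × 0.02 = 1.1 to 57 × 0.05 = 2.9, so about 1 to 3.

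Admissions for other causes among the 380 participants would be additional, but the documents give nothing from which to estimate them. The 57 infections include symptomless seroconversions, so the share admitted could lie below the assumed range.

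**The case against.** The strongest objection is that this is a journal article condensing a full protocol that is said to be available elsewhere. The section refers to definitions set out somewhere, and the complete SAE definition may be wider. That is possible and cannot be settled here. But the article does not leave the criteria out. It states them as a list with a reporting deadline, and the reference to definitions is attached to adverse events, not to the SAE list. If the full protocol is wider, the published sentence misstates it and still needs correcting.

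Four stronger readings are tempting, and the documents do not support them:

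- **Admissions would go unrecorded.** The section sends details of reported events to the SAE form without limiting this to events that meet the three criteria, and hospital stay is collected as an outcome. Recording an event does not, however, class it as serious or start the 48 h clock.
- **The data monitoring committee would be kept uninformed.** The 48 h rule names only the sponsor. The committee's weekly report covers tracker compliance and symptomatic participants and does not depend on SAE status.
- **An SAE table would contradict an outcome that counts admissions.** The outcome is a length of stay, not a count, and the analysis section promises safety summaries without specifying an SAE table. The weaker statement stands: any summary of serious events would inherit the narrow criteria.
- **Every admission of any kind ought to be an SAE.** Nothing in the severity outcomes extends to planned admissions, so their handling has to be stated separately.

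**Conclusion.** The point holds within limits. Taken as written, the SAE criteria do not fit a community population: a new unplanned admission, to a ward or to intensive care, followed by recovery is not an SAE and does not trigger notice to the sponsor. This sits badly with the protocol's own use of hospital and intensive-care stay as severity measures and cost scenarios.

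The consequences are confined to seriousness classification, prompt sponsor notice and any by-arm summary of serious events. The primary outcome, sample size, efficacy analysis and hospital-stay data are unaffected. The number of events concerned is probably small, although when serious events are few each misclassified one weighs more in a comparison of arms.

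The conclusion rests on two readings: that the three criteria form the whole list, and that an admission is not itself one of the sequelae. The illustrative 1 to 3 events rest entirely on the assumed 2–5% admission share.

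**What to change.** Reconcile the Adverse events section with the secondary outcomes, their analysis and the economic evaluation:

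1. Add new inpatient hospitalisation, including intensive care, to the SAE criteria, so that it falls under the existing 48 h sponsor notice.
2. State how planned admissions are to be handled.
3. If the full protocol already contains a wider definition, bring the article's sentence into line with it.
4. Before database lock, check SAE records against the hospital-stay data, so that each admission in the outcome data has been assessed for seriousness.

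The change is about one sentence in the safety section, with a matching check of the SAE form. Its cost is a few more SAE reports and one reconciliation step. Sample size and study visits do not change.

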### Outcomes

#### Primary outcome

Acquisition of COVID-19 infection as confirmed by a positive PCR swab taken at symptom onset or seroconversion during the study

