#### Data management

In the ICE-COVID trial, data collection is performed by trained local research staff and data entry in the REDCap database is completed contemporaneously and in a standardised fashion across two research locations in Swansea, UK. Data will be monitored via an independent data monitoring committee (DMC) using a weekly report to assess compliance with the completion of the daily symptom tracker questionnaire and identify symptomatic participants.

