#### Primary outcome

The primary outcome measure is a binary variable whether COVID-19 infection has been confirmed by PCR swab or not. We will perform a summary analysis reporting the outcome of the categories of two trial arms with respect to the primary outcome measure. The odds ratio and related statistical significance of the chi-square test will be reported. Following on, an adjusted analysis will be done adopting a logistic regression model. The adjustment would be done using the baseline covariates like demographics, co-morbidities (especially history of COVID-19), current medications along with baseline QoLs. The selections of the covariates would be done based on literature reviews along with discussing with the clinical co-applicants involved in this trial. This will also depend on the missing of the covariates and the selection procedure in the statistical modelling.

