### Monitoring

The research project will be coordinated by a Trial Management Group (TMG), consisting of all the named investigators, Joint Clinical Research Facility (JCRF) research nurses and Swansea Trial Unit (STU) researchers. The TMG will meet remotely on a fortnightly basis to oversee the conduct and progress of the research project. An independent Data Monitoring Committee (DMC) will be established to oversee research project progress and ensure high-quality, accurate and valid data collection. Online REDCap data collection will enable real-time monitoring and inbuilt verification and validation as specific data items will link to processes on the ground. The daily tracker questionnaire will allow symptom monitoring and flag up adverse events as well as lack of compliance. An incomplete questionnaire for over 5 days will trigger a telephone call by the research team to the study participant to go through the questionnaire.

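### Tracker symptoms are flagged to the team through a weekly report, which fits poorly with a PCR swab taken at symptom onset and with real-time monitoring

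*Protocol article*

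**What the plan says.** Under Outcomes, the primary outcome is COVID-19 "confirmed by a positive PCR swab taken at symptom onset or seroconversion during the study"; the abstract says the same. The section on the daily symptom tracker gives the tracker the task of picking up symptoms that suggest COVID-19 or another upper respiratory infection.

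Four statements bear on how a symptom reaches the team:

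- Adverse events: the tracker lets participants "report any symptoms that will be flagged up to the research team via a weekly report".
- Data management: the data monitoring committee (DMC) monitors data "using a weekly report to assess compliance with the completion of the daily symptom tracker questionnaire and identify symptomatic participants".
- Adverse events, one sentence before the tracker: "Participants will be encouraged from the outset to contact the research team at the time of an event occurring by telephone or email".
- Monitoring: "Online REDCap data collection will enable real-time monitoring and inbuilt verification and validation". The tracker is also said there to flag adverse events and poor compliance, with no interval given, and "An incomplete questionnaire for over 5 days will trigger a telephone call by the research team".

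Antibodies are tested at the start and end of the study (Seroconversion; End of study treatment), and a change from negative to positive counts as acquired COVID-19. The Statistical analysis section then describes the analysed variable without serology: "The primary outcome measure is a binary variable whether COVID-19 infection has been confirmed by PCR swab or not".

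**The concern.** The tracker is filled in daily and is the trial's systematic means of noticing symptoms, yet the stated interval for passing its content to the team is a week, and it is stated twice. A week is long against a swab defined by symptom onset. REDCap is described as real-time, so nothing in the article suggests that the system imposes the delay. Data management also ties the finding of symptomatic participants to the DMC's report, while Data access limits identifiable data to the direct research team. A case noticed by the committee would therefore have to be passed back before anyone could be contacted.

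The stake is ascertainment of the PCR component. A swab taken well after onset may be negative in a participant who was infected. If serology does not recover that case, a primary event is lost, and the illness could be counted under the secondary outcome for non-COVID respiratory infection.

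**Working it through.** **1. Delay for a participant who relies on the tracker.** Input: a 7-day reporting cycle (Adverse events; Data management). Assumptions: onset is equally likely on any day, and the participant makes no direct contact.

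- Counting whole days: 0 to 6, mean (0+1+2+3+4+5+6)/7 = 3 days.
- Counting continuously: 0 to 7, mean 7/2 = 3.5 days.

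For a participant who telephones, emails or arranges a test at once, this delay does not apply.

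**2. From delay to lost events.** Write the share of infections lost as m = r × f × (1 − s), where r is the share relying on the tracker, f the share of those whose late swab fails to confirm the infection, and s the share recovered by serology. The documents give neither r nor f. For s:

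- PCR or seroconversion (Outcomes): s can be high in those with exit serology and is 0 in those without. The planned loss is 20%, that is 0.20 × 380 = 76 participants, some or all of whom may have no exit sample.
- PCR only (Statistical analysis): s = 0 for everyone.

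Take r × f = 10%, 20% or 30% as an assumed range. If serology recovered every missed case in the 80% who attend, and infections were equally common in those who do not, the loss over all 380 would be 0.10 × 0.20 = 2%, 0.20 × 0.20 = 4% or 0.30 × 0.20 = 6%. Under PCR only it would be the full 10%, 20% or 30%.

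**3. The plan's own sample size.** Inputs from the sample size section: rates 25% and 12.5%, two-sided 5%, power 80%, 1:1. With p̄ = 0.1875 and d = 0.125:

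n per arm = [1.960 × √(2 × 0.1875 × 0.8125) + 0.8416 × √(0.25 × 0.75 + 0.125 × 0.875)]² / 0.125² = (1.0819 + 0.4586)² / 0.015625 ≈ 151.9, so 152 per arm and 304 in total. For loss, 304/0.80 = 380. The stated figures reproduce.

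**4. Power if PCR alone counts and a share m is missed equally in both arms.** Both rates are multiplied by (1 − m), with n = 152 per arm:

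power = Φ{[d√n − 1.960√(2p̄(1 − p̄))] / √(p₁(1 − p₁) + p₂(1 − p₂))}

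For m = 20% the rates are 0.20 and 0.10: (0.10 × √152 − 1.960 × √0.255)/√0.25 = (1.2329 − 0.9898)/0.5 = 0.486, and Φ(0.486) = 68.7%.

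| Share missed (assumed) | Power at 152 per arm | Total for 80% power, before loss |
|---|---|---|
| 0% | 80.0% | 304 |
| 5% | 77.5% | 324 |
| 10% | 74.7% | 346 |
| 20% | 68.7% | 398 |
| 30% | 61.9% | 466 |

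This table applies in full only to the PCR-only reading.

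**The case against.** The strongest reply is that no statement makes the swab wait for the weekly report. The report appears under adverse events and data management, the route from symptom to swab is not described, and a condensed article may leave it to the full protocol, which the article says is available elsewhere. This stands as far as it goes: the absence of a swab procedure is not held against the plan. What remains is a stated interval, given twice, that does not fit two other statements in the same article.

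Several stronger readings are tempting and are not supported:

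- *A case requires a PCR swab.* It does not under Outcomes and Seroconversion, where a change in antibody status is enough.
- *The weekly report is the sole route.* Participants are also encouraged to telephone or email at the time of an event, and the definition of adverse event there is wide enough to take in a fever or cough. No statement says whether such a call leads to a swab.
- *Infections will be misdated.* The primary analysis is binary (chi-square, odds ratio, logistic regression), so dates do not enter it, and daily tracker entries supply symptom onset whenever staff read them.
- *Delays run to about 12 days*, by adding the tracker gap of over 5 days to the weekly cycle. Monitoring says the gap itself triggers a call to go through the questionnaire, so the two do not simply add.
- *The misses favour the active spray.* The Hypothesis section allows for milder illness on the spray, and mild illness may be less likely to prompt a call, so unequal misses are possible. But the trial is double-blind with the same procedures in both arms, and nothing in the article shows such a bias.

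**Conclusion.** The point holds as an inconsistency with a practical consequence. The weekly flag in Adverse events and Data management does not sit well with a swab at symptom onset or with real-time monitoring. A participant who depends on the tracker may be reviewed up to about a week after onset, 3 to 3.5 days on average, and the swab may then miss the infection.

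The size of the harm cannot be fixed from the documents. They give neither the share of participants who depend on the tracker nor the PCR detection rate by day since onset. If PCR or seroconversion is analysed, the exposure is mainly in those without exit serology, up to the planned 20%, and the effect is small. If the PCR-only wording governs, every symptomatic participant is exposed, and missing 10% to 20% of infections would cost about 5 to 11 percentage points of power (80.0% to 74.7% or 68.7%). These figures assume equal misses in both arms and the planned rates. This is a worthwhile, cheap improvement and not a flaw that undermines the trial.

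**What to change.** In Adverse events and Data management, replace the weekly report as the symptom flag with two things: a same-day REDCap alert to the trial team when a qualifying symptom is entered, and an on-screen prompt asking the participant to arrange the PCR swab. Record the swab date beside the onset date from the tracker, so that the interval can be reported by arm. Keep the weekly report for completion rates and DMC oversight, with case-finding assigned to the trial team.

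Reconcile these sections with Outcomes (swab at onset), Monitoring (real-time) and the Statistical analysis section, so that the analysed variable matches the PCR-or-seroconversion definition.

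The cost is one alert rule, one line on the tracker screen, one date field and staff time to read alerts each day. No new visit is needed, and no test beyond the PCR swab that the outcome already calls for.
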